# Effect of vitamin D3-fortified fruit juice supplementation of 4000 IU daily on the recovery of iron status in childbearing-aged women with marginally low iron stores: Protocol for an 8-week, parallel group, double-blind randomized controlled trial

**DOI:** 10.1371/journal.pone.0265772

**Published:** 2022-03-25

## Abstract

**Background:**

In recent years, emerging evidence has highlighted the role of vitamin D as an iron absorption enhancer by suppressing hepcidin concentration, albeit with an unclear underlying mechanism. Dietary-based approach in improving iron status has been widely practised, however, there is a scarcity in randomized controlled trials (RCT) to elucidate the effect of vitamin D-fortified juice on iron status recovery. Therefore, this study aims to investigate the effect of an 8-week vitamin D3-fortified fruit juice supplementation on iron status indicators in childbearing-aged women with marginally low iron stores.

**Methods:**

In a placebo-controlled, double-blind, RCT, a total of 120 women aged between 19–40 with serum ferritin < 20 μg/l and fulfilled the eligibility criteria will be randomized into consuming either vitamin D3-fortified fruit juices containing 4000 IU (100 mcg) (vitamin D) or placebo-fruit juices (placebo) daily for eight weeks. At every 4-week interval, 10 ml fasting blood sample, information on dietary habit and anthropometric measurement will be collected. A mixed model repeated-measures analysis of variance will be performed to determine the effect of the intervention and the interaction with time points for all iron and vitamin D status blood biomarkers.

**Discussion:**

Vitamin D supplementation in food fortification as a novel iron absorption enhancer might be a future and relevant alternative management of iron deficiency as opposed to the oral iron therapy that has poor adherence.

**Trial registration:**

Clinicaltrials.gov: registration number NCT04618289, registration date October 28, 2020, protocol ID JKEUPM-2020-033.

## Introduction

Anemia is one of the most common micronutrient deficiencies, affecting populations worldwide [1]. Half of the time (50%), anemia cases were caused by iron deficiency, leading to multiple negative impacts on human health. A cohesive approach is required to combat this condition since its occurrence is suggested to be multifactorial. Iron supplements have been widely used in at-risk groups, but the efficacy is limited due to its adverse effects, causing low adherence, leading to inefficiency of the intervention [2] and its low bioavailability [3]. Extensive literature, including scientific evidence from systematic reviews, is also available on the effect of dietary-based approach on the improvement of iron status, reporting inconsistent findings [4–11]. Altering individuals’ food preference has been one of the barriers to improving iron status through dietary modification [12], and iron fortification did not completely improved general iron status [13]. A clearer understanding of the interaction between inflammation, erythropoiesis, and hypoxia regulation by the iron regulator peptide hormone, hepcidin, may be useful in designing effective iron interventions that result in fewer adverse effect with maximum advantage [13]. In reference to this, recent studies have presented evidence of the potential utilization of vitamin D as an iron absorption enhancer that suppresses hepcidin, a main iron regulator [14–16]. Besides, observational studies carried out in various settings and populations have suggested an inverse association between increased anemia risk and serum/plasma 25(OH)D concentrations [17].

Despite anemia and vitamin D deficiency being two of the most widespread nutritional problems affecting different age groups across populations, the mechanism that linked these deficiencies remain unclear. There is a scarcity of evidence that supports the links between these deficiencies in the normal population, as previous studies were predominantly carried out in hospital patients [18]. Moreover, it has been suggested that vitamin D plays a role in the erythropoiesis process by decreasing the expression of pro-inflammatory cytokines, which cause the suppression of hepcidin. Consequently, decreased cytokines and suppressed hepcidin leads to higher iron bioavailability for red blood cell (RBC) production and hemoglobin synthesis [19, 20]. It was observed in the in vitro part of a study by Bacchetta, Zaritsky [16] that hepcidin expression was significantly reduced by at least 0.4-fold when treated with 25(OH)D and 1,25(OH)D, whilst Zughaier, Alvarez [20] showed that hepcidin expression was significantly suppressed to between 5 and 10-fold with lipopolysaccharides (LPS) and different concentrations of calcitriol, suggesting direct inhibition of vitamin D metabolites on the transcription of the HAMP gene. A significant reduction of serum hepcidin concentration to 34% and 33% following 24- and 72-hours supplementation of vitamin D2 (100 000 IU) in 7 healthy participants, respectively, was observed in the Bacchetta’s study supporting the in vitro findings, and a moderate but significant negative association between changes in serum hepcidin and 25(OH)D concentrations (r = -0.38, p = 0.02) were observed in 38 kidney patients randomized to receive vitamin D3 (50 000 IU/week), and every other week for 40 weeks or placebo in Zughaier’s.

At present, there is a lack of RCT investigating the effect of vitamin D supplementation using fruit juice as a food fortification vehicle, aiding as an iron absorption enhancer administered routinely, especially in the general population who are at risk of iron deficiency not only in Malaysia but worldwide. Therefore, the present study is designed to determine the effect of an 8-week vitamin D3-fortified fruit juice supplementation on hematological indicators and hepcidin response in a cohort of child-bearing aged Malaysian women with low iron stores, in addition to their habitual dietary intake of iron. In addition to investigating its efficacy, this study also is aimed to assess the effect of a higher dose of vitamin D3 in the fortified fruit juice (4000 IU/day) on iron metabolism. The European Food Safety Authority (EFSA) has set the no-observed-adverse-effect level (NOAEL) of 10 000 IU/day and upper level (UL) of 4000 IU/day for vitamin D, similar to the UL recommendation by the Institute of Medicine (IOM), which is the proposed dose in this study. It was also agreed by the Committee on the toxicity of chemicals in food, consumer products and the environment (COT) that a UL of 4000 IU is appropriate for adults ≥ 18 years and above [21]. It is hypothesized that there will be a significant improvement in hematological indicators following an 8-week daily vitamin D3-fortified fruit juice supplementation in the vitamin D group compared to the placebo group. Furthermore, it is predicted that plasma hepcidin concentration will be reduced, resulting in increased iron stores. Due to the suppressed plasma hepcidin, it is also expected that plasma 25(OH)D concentration will be increased in the vitamin D group as opposed to control group.

## Methods

### Study design and site

The study is a parallel-group, placebo-controlled, double-blind, randomized trial designed to investigate the effect of an 8-week vitamin D3-fortified fruit juice supplementation on hematological indicators and hepcidin response in a cohort of marginally low iron stores, childbearing-aged Malaysian women. The study was registered with the Malaysia National Medical Research Register (NMRR-19-3852-51427), clinicaltrials.gov (NCT04618289), and ethical approval for the study protocol has been obtained from the Universiti Putra Malaysia Ethics Committee for Research Involving Human Subject (JKEUPM) on the 8^th^ May 2020 (JKEUPM-2020-033). The study will be conducted for eight weeks in Selangor, Malaysia, and the data collection will be carried out between July 2021 and July 2022. Participants that will be recruited are childbearing-aged working women residing in urban areas of Serdang, Kajang, Bangi or the vicinity of Selangor state. Potential participants will be recruited from either schools, universities, residential areas or government officials in the specified areas where media such as posters, flyers, emails will be sent to various departments within universities or government officials, discussion boards near residential areas, social media pages and university/government officials’ webpage/intranet.

### Study participants

This study’s inclusion criteria are healthy women of child-bearing age (19–40) and not pregnant or lactating. Candidates with a history of gastrointestinal disorder (celiac disease, Crohn’s disease, irritable bowel syndrome, gastroesophageal reflux disease, peptic ulcers and other related gastrointestinal disorders which may cause nutrient malabsorption) and iron metabolic disorders such as iron overload, had donated blood since the past six months, and regularly consuming nutritional supplements (iron, vitamin D, vitamin C, calcium) will be excluded. Moreover, potential participants must fulfill the screening eligibility criteria: marginally low iron stores and non-anemic.

### Randomization and blinding of participants

The randomization process will be conducted using computer-generated software (www.randomizer.org) by an independent third party. Participants (n = 120) were randomized using permuted block randomization into two groups: vitamin D3-fortified fruit juice (vitamin D group) or placebo-fruit juice (placebo group) in a 1:1 ratio. According to the generated plan, the third party will allocate 62 sachets of vitamin D3-fortified fruit and placebo-fruit juice powder into each supplement container. Each supplement container will then be sealed in a tamper-proof supplement container and numbered before distributed to the participants. Both participants and researcher are double blinded to the group assignment. The numbered supplement will be distributed sequentially to the participants based on the sequence of attendance during their baseline clinic session (Week 0). The blinding will be maintained throughout the study, and allocation will not be unlocked until the end of the data analysis or any adverse event such as hypercalcemia.

### Power and sample size estimation

The sample size was estimated by using (mean ± S.D) serum ferritin concentrations (ug/dl) from a randomized trial carried out by Blanco-Rojo, Pérez-Granados [7] in 41 women aged 18–35 years with low iron stores to determine the effect of iron-fortified fruit juice consumption on iron and vitamin D status. At week 8, it was observed that (mean ± S.D) serum ferritin concentrations were significantly higher in the vitamin D group (34.1 ± 14.8 ug/l), compared to 24.8 ± 17.7 ug/l in the placebo group (p < 0.05). In this study, the effect size is calculated by dividing the mean difference (9.3 ng/ml) with the pooled standard deviation (16.29). With an effect size of 0.571, the total sample size will be required in the present study is 50 individuals/group (Power = 0.80, α err prob = 0.05). By considering a 20% drop-out rate, the total sample size required to demonstrate a significant difference in serum ferritin concentrations between the vitamin D group and placebo is estimated to be 120 (60 participants/group). The sample size was estimated using G-Power Software (Version 3.1.7).

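### The dropout allowance adds 20% to 50 instead of dividing by 0.8, so 60 per group with 20% dropout leaves 48, not the 50 the plan requires

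*Protocol article*

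**What the plan says.** Everything needed is in the protocol article, Methods, Power and sample size estimation.

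- Effect size: "the effect size is calculated by dividing the mean difference (9.3 ng/ml) with the pooled standard deviation (16.29"), which gives 0.571.
- Requirement before dropout: "the total sample size will be required in the present study is 50 individuals/group", with the settings "Power = 0.80, α err prob = 0.05".
- Dropout: "By considering a 20% drop-out rate, the total sample size required to demonstrate a significant difference in serum ferritin concentrations" between the two arms "is estimated to be 120 (60 participants/group").
- Software: "The sample size was estimated using G-Power Software (Version 3.1.7").

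The Abstract, the Randomization and blinding section and the Phase 2 section all repeat 120 as the number randomised. None of them gives a different dropout basis or an added margin.

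**The concern.** A dropout rate is a fraction of those randomised. To finish with a required number, that number must be divided by the fraction expected to stay. The step from 50 to 60 looks like the common slip of adding 20% of the evaluable number, which gives too few.

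At stake is whether the plan's own figures agree. The section is the published justification for 120, and it will probably be carried into the results paper. As written, it tells the reader that 120 women protect the 50-per-group requirement against 20% loss. If dropout ran exactly as planned, the trial would miss its own target while appearing to be on course.

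**Working it through.** **Inputs (all from Power and sample size estimation, except the 1:1 allocation, which is in Randomization and blinding).** Mean difference 9.3; pooled SD 16.29; alpha 0.05; power 0.80; dropout 20%. The article does not say whether the test is one- or two-sided. I took it as two-sided because only that reproduces the stated size.

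**Step 1: reproduce the plan's 50 per group.**

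- d = 9.3/16.29 = 0.571, as stated.
- Two-sample t-test with n per group: degrees of freedom 2n − 2, noncentrality d × √(n/2), power taken from the noncentral t distribution.
- The solution is n = 49.1, so 50 per group. The stated figure reproduces.
- A one-sided test would give 39 per group, which does not match.

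| n per group | Power, two-sided 5%, d = 0.571 |
|---|---|
| 48 | 0.791 |
| 49 | 0.799 |
| 50 | 0.807 |

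Fifty is the smallest whole number that reaches 0.80, so there is no slack in the base figure.

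**Step 2: reproduce the plan's 60 per group.**

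- Adding 20%: 50 × 1.2 = 60. This matches.
- Allowing for 20% loss: 50/(1 − 0.20) = 62.5, so 63 per group, 126 in total. This does not match.

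**Step 3: what 60 per group delivers.**

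- Remaining after 20% loss: 60 × 0.8 = 48 per group, 96 in total, against 50 and 100 required.
- Highest dropout at which 50 remain: 1 − 50/60 = 16.7%.
- Power at 48 per group: 0.791.

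There are two shortfalls on different bases: 2 evaluable women per group (48 against 50), and 3 randomised women per group (60 against 63), which is 6 in total or about 5%.

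**Step 4: could rounding or a different formula explain 60?**

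- No rounding of 62.5 gives 60.
- The normal approximation gives a base of 49 per group. Then 49/0.8 = 61.25, so 62, and 48 is still below 49. Power at 48 by that approximation is 0.799, also just under target.

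**The case against.** The strongest reply is that the slip has almost no consequence. Power falls 0.9 percentage points short of 80%, and no decision in the trial turns on that. The effect size comes from an iron-fortified juice trial in 41 women, and its uncertainty outweighs two women per group. Both points are fair, and they limit how much weight the finding deserves.

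A second reply is that 79.1% describes an unadjusted comparison of completers, not the planned analysis. The Abstract and the Data analysis section plan a repeated-measures analysis over three time points, by intention to treat, with baseline characteristics as covariates. If baseline ferritin is one of them (the text does not say so), residual variance need fall only about 2.3% for 48 per group to reach 80% power: 1 − 48/49.1 ≈ 0.023. That corresponds to a correlation of about √0.023 ≈ 0.15 between baseline and week 8. The documents give no correlation, so this is a threshold and not an estimate for this trial. Women lost after week 4 might also contribute data, although a classical repeated-measures ANOVA may drop incomplete cases, and last observation carried forward is planned only as a sensitivity analysis.

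This stands as a caution about reading 79.1% as the power of the final analysis. It does not repair the sentence. The stated 50 and 80% rest on the same simple comparison, and adding women for dropout already treats dropouts as lost.

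A third reply is that "By considering a 20% drop-out rate" is loose wording and that adding 20% is a common shorthand. Read plainly, though, a dropout rate applies to those enrolled, and on that reading 50 are not retained.

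**Conclusion.** The concern holds. The requirement of 50 per group, the 20% dropout rate and the 60 per group randomised are mutually inconsistent, and the error lies in the dropout step alone. The base calculation is sound for its inputs.

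The size is small: about one percentage point below the power target. It is a certain arithmetic error in a figure the trial relies on, worth correcting, but not evidence of a materially underpowered trial.

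The conclusion rests on a two-sided 5% two-sample t-test at d = 0.571, equal groups, and dropouts contributing nothing to the comparison. Whether 0.571 is a suitable effect size is a separate question and is not judged here.

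**What to change.** Keep 120 and correct the sentence in Power and sample size estimation. Either of these is accurate:

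- Sixty women per group allows for up to 16.7% dropout while retaining 50 per group.
- Sixty women per group with 20% dropout leaves 48 per group, which gives about 79% power for d = 0.571 in a two-sided 5% comparison of the two groups.

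The second keeps the dropout rate the plan chose, so it is the more informative. The cost is one sentence and a slightly less favourable stated figure. Recruitment, supplies, randomisation and analysis stay as they are.

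Randomising 63 per group (126 in total) would also make the figures agree. If screening scaled in proportion to the 736 women planned for 120, six more would mean about 6 × 736/120 ≈ 37 further women screened. For a gain of about one percentage point of power, restating the figure is the proportionate choice.

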### Intervention

#### Vitamin D3-fortified fruit juice supplement and placebo

The vitamin D3-fortified fruit juice powder contains vitamin D3 cholecalciferol (4000 IU, 100 mcg) and packaged in individual sachets (7 g). Both vitamin D3-fortified fruit juice powder and placebo were custom-produced by Fiatec Biosystem Sdn Bhd, Selangor, Malaysia. Matching placebo were produced in the same manner, without the active ingredients by the same company and similar with the intervention powder in terms of appearance, size, colour, and taste to achieve the double-blind design. A sachet of the intervention powder consists of powdered vitamin D3, permitted sweetener Suitena^TM^ containing Xylitol, Erythritol & Stevia, citric acid, anti-caking agent and similar ingredients used to produce placebo juice without the active ingredient of vitamin D3. In addition, a nutritional analysis in a certified laboratory provided the nutritional composition of the vitamin D3-fortified fruit juice powder: 27 kcal energy, 6.8 g carbohydrate, 0.3 g sugars, 7 mg vitamin C, and 0.3 mg iron per sachet.

All vitamin D3-fortified fruit juice powder supplements are packaged in individual sachet for daily consumption and produced as per the research requirement and according to the Good Manufacturing Practice (GMP) standards. For safety purposes, the fruit juice powder was sampled and sent for microbiological testing and heavy metal analysis to be deemed safe for human consumption. These tests were carried out before the powder is packaged into sachets and in the finished products. None of the production cost of both vitamin D3-fortified and placebo-fruit juice powder was financed by the manufacturers. Participants will be provided with an 8-week supply of the fruit juices, depending on the group assigned during the first baseline visit (Week 0). The researcher will demonstrate the fruit juice preparation methods to ensure the use of a standardized method. Additionally, a standard size measuring cup will be provided for all participants, with written instruction on preparing and consuming the fruit juices at home. If participants failed to consume the juice per instruction in any event, it was advised that they do so at once or later in the day and record it in the provided food diary.

#### Adherence to intervention

Participants will be required to consume 56 sachets of vitamin D3-fortified fruit juice or placebo-fruit juice for eight weeks. However, six extra sachets will be provided in each container (n = 62) for researchers to confirm their adherence once the study was completed. Besides, the participants must retain and hand over all the used sachets consumed between week 0 to 4 during the interim clinic session and all the used and unused sachets consumed from week 4 to 8 during the post-intervention clinic to assess the adherence. Adherence to the intervention (%) will be calculated using the following formula: (62 –remaining sachets in the pot upon return)/56 x100. On top of that, participants must record their fruit juice consumption, missed dose and time (if any) as a mean of assessing adherence in the diary provided. Furthermore, participants are also advised to report any adverse effects related to consumption of the fruit juices during each clinic session and communicate with the researcher concerning adverse events they experienced throughout the study.

### Study visits and procedures

Upon recruitment, they were subjected to a screening process to determine their plasma ferritin and hemoglobin concentrations to include women with marginally low iron stores [plasma ferritin concentration < 20 μg/l] [22, 23] and non-anemic [hemoglobin concentration > 12 g/dl] [24]. **Fig 1** outlines the timepoint of enrollment, interventions, and assessments of study, which included two main phases. Phase I involved the recruitment and screening phase, where potential participants with marginally low iron stores will be identified and randomized. After that, Phase II or the intervention phase will be conducted where all the eligible participants will be supplemented with either vitamin D3-fortified fruit juice containing 4000 IU (100 mcg) (vitamin D group) or placebo-fruit juice (placebo group) daily for eight weeks.

**Fig 1 pone.0265772.g001:**
[figure not shown]
Timepoint of study enrollment, interventions and assessments.

#### Phase 1: Recruitment and screening

The prevalence of iron deficiency based on plasma ferritin concentration (< 15 μg/l) in women aged 18–40 years in Malaysia was reported to be approximately 33% [25]. Meanwhile, the prevalence of adult women who consumed vitamin and mineral supplements based on the Malaysian Nutrition Adult Survey (MANS) 2014 was reported to be approximately 32.1% [26]. Considering these data, approximately 736 women would have to be screened to achieve the required sample size. All participants will be provided with a participant information sheet (PIS) and a date for the venous blood collection to ascertain their plasma ferritin and hemoglobin concentrations, to determine their iron stores and hemoglobin levels. Then, they will be provided with a written consent form and will be required to complete a screening questionnaire to ensure the eligibility criteria are met. The screening questionnaire will be used to obtain the participants’ socio-demographic characteristics, including age, ethnicity, religion, educational level, and household income.

During the screening session, 1 ml of venous blood will be collected at the clinical laboratory at the Department of Nutrition, UPM by a trained phlebotomist. The whole blood and plasma sample collected will be used to determine the concentrations of ferritin and hemoglobin. Once the blood analysis results are obtained, participants will be notified via email or phone. Eligible participants with marginally low iron stores and non-anemic will be invited to participate in Phase 2 of the study. On the other hand, those with abnormally high plasma ferritin concentrations (> 150 ug/l) and low hemoglobin concentrations (< 12 g/dl) from the screening will be advised to arrange a check-up with their registered general practitioner and excluded from the study.

